## **8.9 Procedures for assessing safety**

A clinical examination should be performed at screening, week 0 and at all follow-up protocol visits. At each visit any adverse event since the last protocol visit should be recorded (see toxicity

grading table, Appendix 9). Any event fitting the ICH definition of serious (see section 10.1) should be reported to the Trials Unit on an SAE form within one working day of the site being aware of the event. All other adverse events should be reported on the Follow-up CRF.

Further details on reporting of adverse events are presented in section 10.

## **8.10 Long term follow up**

The long-term impact of SCT in HIV-1 infected young people is unknown. Following the young people enrolled in BREATHER for two years after the main trial is completed will provide valuable data on the long-term effects of taking weekends off treatment compared to continuous treatment, and whether there is any long-term impact on subsequent disease progression and efficacy of future treatment.

Routine clinical data will be collected and 12-16 weekly HIV-1 RNA viral load monitoring will be funded for participants in both arms where this is not local standard of care. Adherence questionnaires will be completed every 12-16 weeks (see flowsheet 1.13). A plasma sample and cells (where applicable) will be stored at the annual (48 weeks after the final main study visit) and final long term follow up visit. Management of HIV-1 RNA viral load should continue as specified in appendix 15.

Investigators will continue to be responsible for safety reporting as in the main trial (see section 10).

## **8.11 Trial closure**

### **8.11.1 Planned end of trial**

The main trial will be considered complete after the last patient to be enrolled reaches 48 weeks of follow-up. However, results will not be available for approximately 6 months after completion of the main trial when all data have been received and analysed by the Trials Units. The date of the expected completion of the main trial will be communicated to the participating centres approximately 3-6 months beforehand.

The TSC will continue observational follow-up of all patients enrolled in the trial for a further two years after the main trial is completed providing consent is given. .

The trial will be considered to have ended once all participants have had their final long term follow up visits.

The sponsor, or the sponsor's representative in each country, will notify the national regulatory body and ethics committee of the closure of the trial. The Principal Investigator at each site will be responsible for notifying local ethics boards and any other local bodies, such as R&D departments.

### **8.11.2 Archiving of data**

Data will be stored for 15 years and will be treated in accordance with the UK Data Protection Act of 1998. Blood samples will be shipped to a central storage facility after completion of the sub studies.

## 9 TRANSFER OF YOUNG PEOPLE AND WITHDRAWAL

### 9.1 Participant transfers

For young people moving from the site at which they enrolled to a new site, every effort should be made for them to be followed at the new site and for this site to take over responsibility for the patient. If the site was not listed on the initial CTA, an appropriate Principal Investigator will need to be identified and regulatory and ethics approvals obtained at the new site. A set-up visit will be carried out at the new site and copies of all trial-related documents will be provided. The care giver/participant will need to sign a new consent form at the new site. Until this happens, the follow-up of the patient within the trial remains the responsibility of the recruiting site.

### 9.2 Transition to adult care

Young people recruited between the ages of 16-24 must either be in regular contact with their clinician or be able to transfer to an adult physician at the same site for follow-up or have follow-up at an affiliated adult site (where ethics and R&D have been obtained).

When a young person becomes 18 (or at an earlier age if required by national regulations) during the trial, they must give consent if this has not been gained previously.

### 9.3 Withdrawal from trial intervention

Caregivers and young people have the right to withdraw from the allocated intervention (continuous therapy or short cycle therapy) at any time for any reason. Should a caregiver or young person decide to withdraw from either the protocol and allocated intervention, from routine follow-up data, or withdraw all data, a complete evaluation should be made with an explanation of why the young person is withdrawing, unless consent is specifically withheld. If clinicians wish to withdraw a young person they should discuss this first with the appropriate Trials Unit.

Wherever possible, participants should continue to be followed for clinical and laboratory assessments and information recorded 12 weekly unless the caregiver and the young person explicitly withdraw consent for observational follow-up. If possible the 48 week T-cell subsets and plasma stores should be obtained.

## 10 SAFETY REPORTING

ICH GCP requires that both Investigators and Sponsors follow specific procedures when notifying and reporting adverse events/reactions in clinical trials. These procedures are described in this section of the protocol. Section 10.1 lists definitions, section 10.2-3 gives details of the institution/investigator responsibilities and section 10.4 provides information on the Trials Units' responsibilities (on behalf of the sponsor).

***Please note the changes from previous PENTA protocols on the reporting of HIV-related signs and symptoms: these are now considered AEs or SAEs as appropriate.***

### 10.1 Definitions

The definitions of the EU Directive 2001/20/EC Article 2 based on ICH GCP apply in this trial protocol. These definitions are given in the table below.

**Table 2: Definitions**

| Term                                                                                                                   | Definition                                                                                                                                                                                                                                                                                                                                                                                                                                                                       |
|-------------------------------------------------------------------------------------------------------------------------------|-----------------------------------------------------------------------------------------------------------------------------------------------------------------------------------------------------------------------------------------------------------------------------------------------------------------------------------------------------------------------------------------------------------------------------------------------------------------------------------------|
| Adverse Event (AE)                                                                                                     | Any untoward medical occurrence in a patient or clinical trial subject to whom a medicinal product has been administered including occurrences which are not necessarily caused by or related to that product.                                                                                                                                                                                                                                                                          |
| Adverse Reaction (AR)                                                                                                  | Any untoward and unintended response to an investigational medicinal product related to any dose administered.                                                                                                                                                                                                                                                                                                                                                                          |
| Unexpected Adverse Reaction (UAR)                                                                                      | An adverse reaction, the nature or severity of which is not consistent with the information about the medicinal product in question set out in the summary of product characteristics for that product.                                                                                                                                                                                                                                                                                 |
| Serious Adverse Event (SAE) or Serious Adverse Reaction (SAR) or Suspected Unexpected Serious Adverse Reaction (SUSAR) | Respectively any adverse event, adverse reaction or unexpected adverse reaction that: 
 
• results in death
 
• is life-threatening*
 
• requires hospitalisation or prolongation of existing hospitalisation**
 
• results in persistent or significant disability or incapacity
 
• consists of a congenital anomaly or birth defect
 
• other medically important/clinically significant events***
 
 |

\*The term 'life-threatening' in the definition of 'serious' refers to an event in which the patient was at risk of death at the time of the event; it does not refer to an event which hypothetically might have caused death if it were more severe.

\*\*Hospitalisation is defined as an inpatient admission, regardless of length of stay, even if the hospitalisation is a precautionary measure for continued observation. Hospitalisations for a pre-existing condition (including elective procedures that have not worsened) do not constitute an SAE. Therefore, if an admission is due to a change of HAART regimen without any adverse event, this will not constitute an SAE.

\*\*\*Medical judgement should be exercised in deciding whether an AE/AR is serious in other situations. Important AE/ARs that are not immediately life threatening or do not result in death or hospitalisation but may jeopardise the subject or may require intervention to prevent one of the other outcomes listed in the definition above, should also be considered serious.

Disease progression (refer to appendix 8 for CDC classifications) which meets the seriousness criteria or death as a result of disease progression are now considered to be SAEs and should be reported as a SAE. They should be graded according to the guidelines in the toxicity table (appendix 9) under 'Clinical Symptoms not otherwise specified in this table'.

Any change in social circumstances or admissions to hospital due to such a change will not constitute an SAE.

Pregnancies are notable events and should be reported on an SAE form.

## 10.2 Institution/Investigator Responsibilities

All SAEs and pregnancies must be reported by the investigator to the appropriate Trials Unit on a Serious Adverse Event (SAE) form within one working day of the investigator being aware of the event. **The investigator has a responsibility to report all such events for the entire duration of follow up in the trial.**

All other AEs/ARs should be reported on the follow-up forms.

The severity (i.e. intensity) of all AEs/ARs (serious and non-serious) in this trial should be graded using the toxicity gradings in Appendix 9.

Where a pregnancy event has occurred in a participant on SCT, the participant should be instructed to return to continuous therapy.

## 10.3 Investigator Assessment

### (a) Seriousness

When an AE/AR occurs the investigator responsible for the care of the patient must first assess whether the event is serious using the definition given in Table 2. If the event is serious, then an SAE form must be completed and the Trials Unit notified.

### (b) Causality

The Investigator must assess the causality of all serious events/reactions in relation to the trial therapy using the definitions in Table 3. There are 5 categories: unrelated, unlikely, possible, probable and definitely related. If the causality assessment is unrelated or unlikely to be related the event is classified as a SAE. If the causality is assessed as either possible, probable or definitely related then the event is classified as a SAR. If a drug is at least possibly related to an AE, this should be noted on the follow up form.

### (c) Expectedness

If the event is a SAR the Investigator must assess the expectedness of the event. If a SAR is assessed as being unexpected it becomes a SUSAR. The definition of an unexpected adverse reaction (UAR) is given in Table 3 and is one not previously reported in the current summary of product characteristics. Please see manual of operating procedures for a summary of expected toxicities.

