**Table 3: Definitions of causality**

| Relationship     | Description                                                                                                                                                                                                                                                                                                     | Event Type |
|------------------|-----------------------------------------------------------------------------------------------------------------------------------------------------------------------------------------------------------------------------------------------------------------------------------------------------------------|------------|
| Unrelated | There is no evidence of any causal relationship                                                                                                                                                                                                                                                                 | SAE        |
| Unlikely  | There is little evidence to suggest there is a causal relationship (e.g. the event did not occur within a reasonable time after administration of the trial medication). There is another reasonable explanation for the event (e.g. the patient's clinical condition, other concomitant treatment).            | SAE        |
| Possible  | There is some evidence to suggest a causal relationship (e.g. because the event occurs within a reasonable time after administration of the trial medication). However, the influence of other factors may have contributed to the event (e.g. the patient's clinical condition, other concomitant treatments). | SAR        |
| Probable  | There is evidence to suggest a causal relationship and the                                                                                                                                                                                                                                                      | SAR        |

|                   |                                                                                                                    |     |
|-------------------|--------------------------------------------------------------------------------------------------------------------|-----|

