**Notification Procedure:**

1. The SAE form must be completed by the Investigator (consultant named on the signature list and delegation of responsibilities log who is responsible for the patient's care), with due care being paid to the grading, causality and expectedness of the event as outlined above. In the absence of the responsible investigator the form should be completed and signed by a member of the site trial team. The responsible investigator should subsequently check the SAE form, make changes as appropriate, sign and then re-fax to the appropriate Trials Unit as soon as possible. The initial report shall be followed by detailed, written reports as appropriate.
2. Send the SAE form by fax to the appropriate Trials Unit:
 

|                                                                            |                                                                                                                                |
|----------------------------------------------------------------------------|--------------------------------------------------------------------------------------------------------------------------------|
| MRC Clinical Trials Unit
INSERM SC10-US019
PHPT | Fax Number: [name]
Fax Number: [name]
Fax Number: [name] |
|----------------------------------------------------------------------------|--------------------------------------------------------------------------------------------------------------------------------|
3. Follow-up of events: Patients must be followed-up until clinical recovery is complete and laboratory results have returned to normal or baseline, or until the event has stabilised. Follow-up should continue after completion of protocol treatment if necessary. Follow-up information should be noted on a further SAE form by ticking the box marked 'follow-up' and faxing to the appropriate Trials Unit as information becomes available. Extra annotated information and/or copies of test results may be provided separately. The patient must be identified by trial number and date of birth only. The patient's name should not be used on any correspondence.
4. Staff at the institution must notify their local research ethics committee of the event (as per the institution's standard local procedure).

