**10.4 Trials Units' responsibilities**

Medically qualified staff at the Trials Units and the Chief Investigator (or a medically qualified delegate) will review all SAE reports received. The causality assessment given by the local Investigator at the hospital cannot be overruled and in the case of disagreement, both opinions will be provided in any subsequent reports.

The MRC Clinical Trials Unit at UCL, INSERM SC10 and PHPT are undertaking the duties of trial sponsor and are responsible for pharmacovigilance in the countries they co-ordinate and are responsible for the reporting of SUSARs and other SARs to the regulatory authorities of countries in which the trial is taking place and the national research ethics committees as appropriate. In certain instances this responsibility will be delegated to a national co-ordinator.

The Trials Units will also keep all investigators informed of any safety issues that arise during the course of the trial.

Trials Units will comply with any further reporting requirements of the countries they co-ordinate.

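### Section 10.3(c) leaves severity out of the test for an unexpected reaction and points to the wrong table, so a listed reaction that is worse than labelled may be classed as expected at site

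*Combined protocol and SAP*

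**What the plan says.** Section 10.1 states that "The definitions of the EU Directive 2001/20/EC Article 2 based on ICH GCP apply in this trial protocol" and sets those definitions out in Table 2. There an unexpected adverse reaction is "An adverse reaction, the nature or severity of which is not consistent with the information about the medicinal product in question", judged against that product's SmPC.

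Section 10.3 then takes the investigator through seriousness, causality and expectedness in turn. Under (c) it says of the definition: "unexpected adverse reaction (UAR) is given in Table 3 and is one not previously reported in the current summary of product characteristics". The consequence follows directly: "If a SAR is assessed as being unexpected it becomes a SUSAR". The table it names is headed "Table 3: Definitions of causality".

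The notification procedure has the investigator complete the serious adverse event (SAE) form "with due care being paid to the grading, causality and expectedness of the event as outlined above".

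Section 10.2 provides that "All SAEs and pregnancies must be reported by the investigator to the appropriate Trials Unit" within one working day. Under section 10.4, medically qualified Trials Unit staff and the Chief Investigator or a delegate review all SAE reports. "The causality assessment given by the local Investigator at the hospital cannot be overruled"; nothing comparable is said about expectedness. The Trials Units report both SUSARs and other serious adverse reactions (SARs) to the regulators.

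**The concern.** The protocol contains two tests for the same classification, and they are not equivalent. The shorter one, which omits severity, stands in the step-by-step instruction that an investigator is likely to have open when filling in the SAE form. Its pointer leads to a table that cannot correct it.

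What is at stake is the label attached to a SAR whose type is in the SmPC but which turns out worse than the SmPC describes. If the site calls it expected, it does not become a SUSAR at that step, and handling as a SUSAR may be missed or start late. The trial enrols from age 8, and section 10.2 keeps the reporting duty in force throughout follow-up. Sites are spread over several countries and three Trials Units, so two readings could also produce inconsistent classification between them.

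**Working it through.** No arithmetic applies and the plan states no figure to reproduce. The check is a comparison of texts.

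**Step 1: the two tests.**
- Table 2 has two limbs, nature and severity. A mismatch with the SmPC on either one makes the reaction unexpected.
- Section 10.3(c) has one: whether the reaction has previously been reported in the SmPC. Severity is not mentioned.

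**Step 2: apply both to each type of SAR.**

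| SAR | Table 2 | 10.3(c), read literally |
|---|---|---|
| Type not in the SmPC | Unexpected | Unexpected |
| Type in the SmPC, severity as labelled | Expected | Expected |
| Type in the SmPC, more severe than labelled | Unexpected | Expected |

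The tests differ in the third row only.

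**Step 3: follow the cross-references in section 10.3.**
- (a) Seriousness cites Table 2, which is correct.
- (b) Causality cites Table 3, which is correct.
- (c) Expectedness cites Table 3, which lists five causality categories and contains no definition of an unexpected reaction. The definition is in Table 2.

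A reader who follows the pointer in (c) does not reach the severity limb and is left with the shortened description.

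**Step 4: does the site's answer matter?** Yes. Section 10.3(c) makes it decide whether a SAR becomes a SUSAR, and the notification procedure refers back to the assessment steps above it. Severity is already graded for every event under section 10.2 and Appendix 9, but 10.3(c) does not ask for it to be compared with the SmPC.

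**Step 5: what happens afterwards?** Every SAE reaches the Trials Unit whatever its expectedness, and every report gets a medical review. Section 10.4 bars the reviewers from overruling causality only, so they are free to take a different view of expectedness. It does not say that they re-assess it, or what happens if they disagree with the site.

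**The case against.** The best defence is that this is a mis-numbered pointer followed by an incomplete paraphrase. Section 10.1 keeps the Table 2 definitions in force, 10.3(a) sends the same investigator to Table 2 a few lines earlier, and 10.3(c) itself says that the definition lives in a table. Behind the site stand one-working-day reporting of all SAEs, central medical review, regulatory reporting that also covers other SARs, and review by the data monitoring committee about every six months. The safety outcomes, such as grade 3 or 4 events, do not depend on expectedness. Figure 1 is not shown and the manual of operating procedures is not among the documents, so either may restate the full criterion.

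Most of this stands, and it limits the consequence. It rules out the stronger reading that a reader might infer: that a reaction counts as unexpected only if it is absent from the SmPC, so that every listed but more severe reaction is misclassified and never becomes a SUSAR. Section 10.3(c) does not contain the word only, Table 2 is not displaced, and nothing stops a central reviewer from reclassifying the event.

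The defence does not remove the inconsistency. That Table 2 governs is the reason 10.3(c) is wrong as worded. A medical review with no stated expectedness check may catch the error, but the protocol does not say that it will.

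**Conclusion.** The point holds as an internal inconsistency in a safety-classification rule. Section 10.3(c) omits the severity limb of the governing definition and cites the wrong table. The supportable consequence is a risk: a listed reaction that exceeds its labelled severity may be called expected at site, and its handling as a SUSAR may be missed or delayed.

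The size cannot be put in numbers. The affected class is exactly the third row of the comparison, but the documents give no expected number of such events and contain no SmPC from which to judge how often they could arise. The conclusion assumes that some investigators apply 10.3(c) as written without going back to Table 2. The point about delay also assumes that SUSARs are handled faster than other SARs; the available text distinguishes the two but gives no regulatory timelines for either. No estimand, sample size, error rate or analysis is affected.

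**What to change.** Reconcile section 10.3(c) with Table 2 by two edits to the same sentence:
- Change the cross-reference from Table 3 to Table 2.
- Replace the shortened description so that a reaction is unexpected when *either its nature or its severity* is inconsistent with the current SmPC.

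Check that Figure 1 and the manual of operating procedures use the same criterion. The sponsor could also state in section 10.4 who checks expectedness during the central review, but this is optional: the inconsistency is resolved without it.

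The cost is one sentence in the protocol and possibly a few more events handled as SUSARs.
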